## Abstract

**Background:**

Coronary computed tomography angiography (CCTA) allows for non-invasive assessment of obstructive coronary artery disease (CAD) beyond measures of stenosis severity alone. This assessment includes atherosclerotic plaque characteristics (APCs) and calculation of fractional flow reserve (FFR) from CCTA (FFR_CT_). Similarly, stress imaging by myocardial perfusion scintigraphy (MPS) provides vital information. To date, the diagnostic performance of integrated CCTA assessment versus integrated MPS assessment for diagnosis of vessel-specific ischemia remains underexplored.

**Methods:**

CREDENCE will enroll adult individuals with symptoms suspicious of CAD referred for non-emergent invasive coronary angiography (ICA), but without known CAD. All participants will undergo CCTA, MPS, ICA and FFR. FFR will be performed for lesions identified at the time of ICA to be ≥40 and <90 % stenosis, or those clinically indicated for evaluation. Study analyses will focus on diagnostic performance of CCTA versus MPS against invasive FFR reference standard. An integrated stenosis-APC-FFR_CT_ metric by CCTA for vessel-specific ischemia will be developed from derivation cohort and tested against a validation cohort. Similarly, integrated metric by MPS for vessel-specific ischemia will be developed, validated and compared. An FFR value of ≤0.80 will be considered as ischemia causing. The primary endpoint will be the diagnostic accuracy of vessel territory-specific ischemia of integrated stenosis-APC-FFR_CT_ measure by CCTA, compared with perfusion or perfusion–myocardial blood flow stress imaging testing, against invasive FFR.

**Discussion:**

CREDENCE will determine the performance of integrated CCTA metric compared to integrated MPS measure for diagnosis of vessel-specific ischemia. If proven successful, this study may reduce the number of missed diagnoses and help to optimally predict ischemia-causing lesions.

**Trial registration:**

ClinicalTrials.gov, NCT02173275. Registered on June 23, 2014.

**Electronic supplementary material:**

The online version of this article (doi:10.1186/s12872-016-0360-x) contains supplementary material, which is available to authorized users.

## Background

Coronary revascularization remains a mainstay of treatment for coronary artery disease (CAD), which continues to affect more than 16 million US adults. Functional myocardial ischemia may result from anatomically obstructive CAD and strongly determines prognosis, and thus is useful for guiding decisions of revascularization [1, 2]. Invasive fractional flow reserve (FFR) is the reference standard for determining the physiologic significance of CAD for vessel-specific ischemia among patients with multi-vessel CAD. However, the invasive nature of FFR measurement limits this evaluation to only high-risk patients with indications for ICA.

Until now, for the vast numbers of patients at low or intermediate risk for CAD, numerous non-invasive stress imaging modalities including echocardiography, cardiac magnetic resonance (CMR), and myocardial perfusion scintigraphy (MPS) have served as a mainstay for identifying ischemia by detecting stress-induced regional myocardial perfusion defects, of which the most commonly employed is MPS [3, 4]. At a per-patient level, MPS by single photon emission computed tomography (SPECT) or positron emission tomography (PET) is capable of determining the severity and extent of myocardial ischemia with high performance [5, 6]. However, the ability of MPS to correctly discriminate ischemia on a per-vessel basis is less robust [7]. Further, the accuracy of MPS is compromised in patients with multi-vessel CAD [8]. These findings therefore raise questions regarding the ability of MPS to correctly identify coronary lesions that would benefit from revascularization [9].

In the recent past, coronary computed tomography angiography (CCTA) has emerged as a promising non-invasive imaging modality for the diagnosis of anatomically obstructive CAD, with high sensitivity and negative predictive value compared to ICA [10, 11]. Although CCTA enables discrimination of stenosis with high accuracy, it can overestimate stenosis, and similar to ICA, may misidentify ischemia [12]. These findings have led to the emergence of several methods using CCTA-specific data beyond luminal stenosis severity alone for the diagnosis of lesion-specific ischemia. These methods include additional atherosclerotic plaque characteristics (APCs) and calculation of FFR from CCTA (FFR_CT_).

APCs assessment by CCTA has demonstrated high agreement with invasive methods of plaque assessment and has shown to improve discrimination of ischemia-causing coronary lesions [13]. These include plaque burden and composition, and arterial remodeling [14, 15]. Previous studies have reported that selected APCs are also associated with ischemia by MPS [16, 17]. Yet, the entirety of APCs to optimize the precise identification of ischemia-causing culprit lesions has not been examined to date.

FFR_CT_ represents a novel non-invasive imaging technique that can evaluate the physiologic significance of CAD and enables the calculation of vessel-specific FFR [18]. Further still, given the computational modeling technique in FFR_CT_ calculations, it is possible to place a “virtual stent” by modeling the resolution of luminal compromise. In a recent prospective multicenter study, FFR_CT_ was found to be superior to CCTA stenosis alone for diagnosis of ischemia-causing lesions, and demonstrated good correlation with FFR [19].

Similar to CCTA, which can provide important information beyond luminal stenosis severity alone, stress imaging testing can also do so by an array of prognostically and diagnostically important factors. These include high-risk imaging features (e.g., transient ischemic dilation, stress-induced lung uptake of radiotracer, increased right ventricular uptake), myocardial blood flow (MBF), exercise electrocardiographic (ECG) findings, functional capacity, stress-induced symptom complexes. Even within these categories, other more granular data are available, e.g., in ECG data, extent of ST-segment depression, rate-pressure product, heart rate recovery, and other variables are well known to augment CAD diagnosis.

The overall objective of the CREDENCE trial is to determine the utility of a novel diagnostic integrated approach by integrating anatomic APCs with physiologic FFR_CT_ to optimize the precise identification of vessel-specific ischemia by CCTA, and to compare this measure against the totality of relevant variables by MPS.

## Methods/Design

The Computed TomogRaphic Evaluation of Atherosclerotic DEtermiNants of Myocardial IsChEmia (CREDENCE) trial (clinicaltrials.gov NCT02173275) is a prospective multicenter cross-sectional study of 618 individuals (*n* = 309 [derivation cohort]; *n* = 309 [validation cohort]) wherein eligible participants will undergo CCTA, MPS, ICA and FFR. For the purposes of the study, either MPS, CCTA, and/or FFR will have been performed for clinical purposes, with the other test being performed as part of the trial procedure. Study analyses will focus on the diagnostic performance of MPS versus CCTA against the gold standard of invasively determined FFR for vessel-specific ischemia.

The relationships of anatomic APCs and physiologic FFR_CT_ by CCTA will be assessed according to measures of vessel-specific ischemia, referenced to an invasive FFR standard. An integrated anatomic-physiologic metric by CCTA for vessel-specific ischemia will be developed from a derivation cohort and tested against a validation cohort, both of which will undergo CCTA, MPS, ICA and FFR. Similarly, an integrated metric by MPS for vessel-specific ischemia will be developed and validated. The performance of this integrated CCTA measure will be directly compared with MPS for diagnosis of vessels that manifest ischemia. The schematic summary of the trial design is depicted in Fig. 1.

**Fig. 1 Fig1:**
[figure not shown]
CREDENCE study design. CAD, coronary artery disease; ICA, invasive coronary angiography; CCTA, coronary computed tomography angiography; MPS, myocardial perfusion scintigraphy; FFR, fractional flow reserve; FFR_CT_, fractional flow reserve derived from coronary computed tomography angiography; APCs, atherosclerotic plaque characteristics; PCI, percutaneous coronary intervention

Importantly, for reasons of safety, all FFRs to be performed will be limited to lesions identified at the time of ICA to be ≥40 and <90 % stenosis, or those that should be clinically indicated for evaluation. As lesions <40 % in diameter stenosis severity are almost uniformly non-ischemic and those ≥90 % are typically ischemic, these lesions should be avoided for interrogation with an FFR guidewire for reasons of patient safety, unless deemed medically necessary. In contrast, coronary stenoses between 40 and 90 % demonstrate variable rates of ischemia and may be appropriately interrogated for clinical indications. If FFR interrogation of a coronary lesion between 40 and 90 % is considered as imparting excess risk to a study subject for anatomical or other reasons, it will be avoided. In keeping with prior studies, vessel territories will be comprised of the left anterior descending artery [LAD] (and diagonal branches), the left circumflex artery [LCx] (and obtuse marginal branches), and the right coronary artery [RCA] (and posterolateral branch and posterior descending artery). Patients who undergo percutaneous coronary intervention (PCI) by intracoronary stenting of ≥1 coronary lesions after the ICA and FFR measurements may have repeat measurements of FFR after the completion of stent deployment, as clinically indicated.

The CREDENCE study will be performed in 19 investigative sites in USA, Canada, Netherlands, Japan, China, Latvia, Italy, and South Korea (ClinicalTrials.gov, NCT02173275). Each center may not enroll more than 40 % of the total number of subjects. The shortest time duration between noninvasive and invasive testing will be at the discretion of the local physician. The maximum time permitted between noninvasive and invasive tests will be 60 days.

## Study objectives

### Primary objective

The primary objective is to determine the diagnostic accuracy of vessel territory-specific ischemia by use of an integrated stenosis-APC-FFR_CT_ measure determined by CCTA, when compared with perfusion or perfusion–MBF stress imaging testing, against invasive FFR. Stress imaging will also include additional characteristics, as described above, which do not exhibit co-linearity with other variables. CCTA and stress imaging features will be hierarchically evaluated: CCTA will be evaluated by stenosis, then FFR_CT_, then APCs; while stress imaging will be evaluated by perfusion, then MBF, then ECG features and finally, functional capacity.

### Secondary objectives

The secondary objective is to compare the accuracy of the individual components of the CCTA and MPS measures to detect ischemia by invasive FFR: APC components; FFR_CT_; MPS vessel-specific perfusion deficits; and reduced MBF. Another objective is to determine the accuracy of FFR_CT_ “virtual stenting” with a post-PCI FFR value of >0.80 in an effort to assess the correlation between FFR_CT_ “virtual stenting” to post-PCI FFR.

## Target population

The CREDENCE target population will comprise a large and representative sample of individuals for whom CCTA and MPS testing confer the largest potential benefit; that is, for those with suspected CAD who are being referred for non-emergent clinically indicated ICA based upon an imaging study (either MPS or CCTA). In this regard, CREDENCE will enroll adult individuals who meet the inclusion criteria and none of the exclusion criteria, as detailed in Table 1. The study is considered non-significant risk because all subjects will undergo clinically-indicated ICA as planned, with FFR performed in vessel territories with >40 % stenosis for which there is equipoise of ischemia presence [20].

**Table 1 Tab1:** CREDENCE trial inclusion and exclusion criteria

*Inclusion criteria*	
(1) Age ≥18 years	
(2) Patients scheduled to undergo clinically-indicated non-emergent invasive coronary angiography	
*Exclusion criteria*	
(1) Known coronary artery disease (myocardial infarction, percutaneous coronary interventions, coronary artery bypass graft)	
(2) Hemodynamic instability	
(3) Inability to provide written informed consent	
(4) Concomitant participation in another clinical trial in which an individual is subject to investigational drug or device	
(5) Pregnancy or unknown pregnancy status	
(6) Absolute contraindication to iodinated contrast due to prior near-fatal anaphylactoid reaction (laryngospasm, bronchospasm, cardiorespiratory collapse, or equivalent)	
(7) Impaired chronic renal function (serum creatinine ≥1.7 mg/dl or Glomerular Filtration Rate <30 ml/min)	
(8) Baseline irregular heart rhythm (e.g., atrial fibrillation, etc.)	
(9) Heart rate ≥100 beats per minute	
(10) Systolic blood pressure ≤90 mm Hg	
(11) Contraindications to β blockers or nitroglycerin or adenosine	

## Efficacy analyses and sample size

### Primary efficacy analysis

The primary statistical analysis will be diagnostic accuracy of vessel territory-specific ischemia using an integrated APC-FFR_CT_ metric by CCTA, as compared with territory-specific ischemia on perfusion or perfusion-MBF stress imaging, against invasive FFR. Three vessel territories including the LAD, LCx, and RCA will be examined. The non-ischemic vessels will serve as controls to ischemic vessels. An FFR measurement cutoff value of ≤0.80 will be considered as ischemia-causing, and >0.80 as non ischemia-causing.

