### Analysis of APCs and FFR_CT_ against an invasive FFR standard

APCs and FFR_CT_ will be assessed against an invasive FFR standard for diagnosis of lesion-specific ischemia. Direct comparison of an integrated APC-FFR_CT_ metric to a non-invasive gold standard by a composite perfusion, MBF, ECG, and functional capacity metric will then be made.

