### (C) Derivation and validation of an integrated anatomic-physiologic CCTA metric for diagnosis of ischemia

An integrated CCTA metric will then be developed that will represent the most parsimonious set of APCs for improving diagnosis of vessel-specific ischemia. The weighted APC set will be combined to FFR_CT_ values using information derived from (A) and (B). Multivariate mixed-effects logistic regression analyses will be conducted with APC-FFR_CT_ measures as a predictor of ischemia. A backward stepwise selection method will be used so that only significant variables at *p* < 0.05 level will be included in the final model. Since these analyses are on a per-vessel basis, a random effects model will be used to account for within-patient clustering. Finally, a summary APC-FFR_CT_ metric as a predictor of ischemia, accounting for the weighted contribution of APCs and FFR_CT_, will be obtained. This summary APC-FFR_CT_ metric will be tested for its ability to diagnose vessel-based ischemia in a validation cohort of 309 patients who will also undergo CCTA, MPS, ICA, and FFR.

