### (D) Comparison of an integrated anatomic-physiologic CCTA metric to vessel-territory specific ischemia by MPS

In the validation cohort, the integrated APC-FFR_CT_ metric will be directly compared against MPS for the diagnosis of vessel-specific ischemia, using invasive FFR as a reference standard. This integrated metric will be compared against a combined perfusion-MBF-ECG-functional capacity measure by MPS so as to assure the highest diagnostic performance of both CCTA and MPS in comparison. MBF is anticipated to be most useful in the presence of balanced reduction of perfusion (i.e., in the absence of relative perfusion differences) and thus, is expected to increase specificity when a regional vessel-based territory appears normal by perfusion.

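### The primary contrast is stated inconsistently: the CCTA metric appears with and without stenosis, and the MPS comparator appears as perfusion, perfusion-MBF or a four-part composite

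*Protocol article*

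**What the plan says.** **CCTA metric.** In the Abstract (Methods), "The primary endpoint will be the diagnostic accuracy of vessel territory-specific ischemia of integrated stenosis-APC-FFR_CT_ measure by CCTA". The Primary objective likewise refers to an "integrated stenosis-APC-FFR_CT_ measure determined by CCTA" and sets an order of evaluation: "CCTA will be evaluated by stenosis, then FFR_CT_, then APCs". The Primary efficacy analysis, section (C) on derivation and validation, section (D) on the comparison with MPS, and the Discussion all speak of an APC-FFR_CT metric, without stenosis in its name. Section (C) fits a mixed-effects logistic model to APC and FFR_CT measures. On selection it says: "A backward stepwise selection method will be used so that only significant variables at" the 0.05 level stay in the final model.

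**MPS comparator.** In the Primary efficacy analysis the CCTA metric is assessed "as compared with territory-specific ischemia on perfusion or perfusion-MBF stress imaging, against invasive FFR". The Abstract's endpoint sentence gives the same alternatives. So does the first sentence of the Primary objective, which then adds further stress-imaging characteristics and lists ECG features and functional capacity. Section (D) differs: "This integrated metric will be compared against a combined perfusion-MBF-ECG-functional capacity measure by MPS". The Discussion names the same four parts.

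**Reference.** Methods/Design, the Primary efficacy analysis and section (D) use invasive FFR. The section on analysing APCs and FFR_CT against an invasive FFR standard compares the CCTA metric "to a non-invasive gold standard by a composite perfusion, MBF, ECG, and functional capacity metric".

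**The concern.** The Discussion states a superiority hypothesis for integrated CCTA over integrated MPS. Such a test needs one index test, one comparator and one reference. Here the index test changes between the objective and the analysis, and the comparator changes between the primary analysis and the section that describes the comparison.

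Two things are at stake. First, an analyst who follows the Primary efficacy analysis and section (C) literally would test a CCTA metric other than the one in the endpoint, possibly against a weaker MPS measure than the one section (D) calls for. Second, while several versions can each be called primary, the nominal error level holds only if the choice is made before the results are seen, and this article does not record that choice.

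**Working it through.** **1. The statements side by side**

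| Section | CCTA metric | MPS comparator |
|---|---|---|
| Abstract, primary endpoint | stenosis, APCs, FFR_CT | perfusion, or perfusion with MBF |
| Primary objective | stenosis, APCs, FFR_CT | perfusion, or perfusion with MBF; then ECG features and functional capacity added |
| Primary efficacy analysis | APCs, FFR_CT | perfusion, or perfusion with MBF |
| Analysis of APCs and FFR_CT against an invasive FFR standard | APCs, FFR_CT | four-part composite |
| Section (C), model building | APCs, FFR_CT | not addressed |
| Section (D), validation cohort | APCs, FFR_CT | four-part composite |
| Discussion | APCs, FFR_CT | four-part composite |

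**2. Could APC-FFR_CT be shorthand that already contains stenosis?** The section on atherosclerotic plaque characteristics lists six: low attenuation plaque, positive remodeling, mixed plaque, plaque burden, minimal luminal area and transluminal attenuation gradient. Minimal luminal area carries part of the stenosis information. It is not the graded stenosis described under CCTA image acquisition and interpretation, and the Primary objective lists stenosis as a step separate from APCs. So the model in section (C), as written, does not produce the metric named in the endpoint.

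**3. Direction of the comparator choice.** Section (D) justifies the four-part composite as the way to give both tests their best performance. The Discussion says that comparisons leaving out MBF, ECG and functional capacity tilt towards CCTA. On that reasoning, perfusion alone, which the Primary efficacy analysis allows, is the easier comparator to beat.

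**4. Size, if the best version could be reported.** The article gives no figure to reproduce here. Its sample-size section concerns an odds ratio of 2.0 in a logistic regression and names no comparator.

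Inputs: 2 CCTA versions × 3 MPS versions = 6 contrasts. The 0.05 level is in the sample-size section; its sidedness is not stated. I take it as two-sided, so 0.025 in favour of CCTA (z > 1.96). The correlation r between the test statistics is an assumption, taken as equal for all pairs.

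Model: all true differences are zero, and Z_i = √r·U + √(1−r)·E_i with independent standard normal U and E_i. Then, with Φ and φ the standard normal distribution function and density,

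P(at least one Z_i > 1.96 among k) = 1 − ∫ Φ[(1.96 − √r·u)/√(1−r)]^k φ(u) du.

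Chance of a false result in favour of CCTA:

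| r | k = 2 (perfusion; perfusion-MBF) | k = 3 (three MPS versions, one CCTA metric) | k = 6 |
|---|---|---|---|
| 0.95 | 3.2 % | 3.7 % | 4.4 % |
| 0.9 | 3.5 % | 4.2 % | 5.4 % |
| 0.8 | 3.9 % | 4.9 % | 6.9 % |
| 0.7 | 4.2 % | 5.5 % | 8.2 % |
| 0.5 | 4.5 % | 6.3 % | 10.4 % |

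A simulation of the same model with 200,000 replicates agrees with these values to about 0.1 percentage point. For independent tests the six-version figure would be 1 − 0.975^6 = 14.1 %. The versions share vessels, reference and components, so the higher correlations are more plausible.

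The calculation supposes that no contrast truly differs. It does not cover the case in step 3, where CCTA truly beats perfusion alone but not the composite. There the problem is that an easier question has been answered, and no error rate measures it.

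**The case against.** **The text leans towards one comparator.** Section (D) places the comparison in the validation cohort, names the composite and gives the reason. The Primary objective lists the same four parts, the hypothesis is integrated against integrated, and single components are secondary. This stands as evidence of intent, and it is why the fix below adopts the composite. It does not remove the contradiction, because the section headed as the primary analysis and the endpoint sentence still say something narrower.

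**The word 'or' may describe modality, not choice.** Under Myocardial perfusion scintigraphy, PET is used when possible and yields MBF; SPECT, where PET cannot be done, evaluates perfusion. The alternatives may simply be what each patient's scan provides. That is plausible, though nowhere stated, and if it is right the two-comparator column above does not describe a real choice. It would not explain the four-part composite.

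**The count of six is generous.** The stenosis version against the composite appears only if the additions in the Primary objective are read as part of the comparator. The correlations are not in the article either.

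**Stronger readings to resist.** A reader might infer that hierarchical evaluation and backward selection exclude each other. They can coexist: ordered evaluation across blocks, selection within the APC-FFR_CT model. Section (C) also describes a final metric that weights both APCs and FFR_CT, so dropping FFR_CT is not the stated intent, although the literal p-value rule does not protect it. A reader might infer that the gold-standard phrase makes CCTA superiority impossible. It is loose wording for the comparator, since the analysis sections keep invasive FFR as reference; the Discussion uses the same term for stress testing, with the word gold in quotation marks. A reader might also infer that the test will be chosen after the results. The article only fails to prevent this, and an unseen SAP or full protocol may do so.

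**Conclusion.** The inconsistency is in the text and does not depend on any missing document. The endpoint and objective include stenosis, while the primary analysis and model building do not name it. The primary analysis also allows a narrower MPS comparator than section (D) says is needed for a fair comparison. The article does not say which version is primary.

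The effect on error cannot be fixed from the document. Under the best-of-six assumption it is about 4 to 10 % in favour of CCTA against 2.5 %, for assumed equal correlations of 0.95 to 0.5. Overlap between the metrics points towards the lower end, and fewer real alternatives would reduce it further. The main weight of the point is on the definition of the primary test, with the error rate as a secondary illustration. This is a should-fix point.

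**What to change.** - In the Abstract, Primary objective, Primary efficacy analysis, the section on APCs and FFR_CT against an invasive FFR standard, and sections (C) and (D), name one primary contrast in the validation cohort, with invasive FFR as the sole reference: the integrated CCTA metric versus the integrated four-part MPS metric of section (D).
- State whether stenosis is in or out of the CCTA metric. If in, list it as a candidate in section (C).
- State how patients without MBF (SPECT) enter the MPS metric.
- Label the perfusion-only and perfusion-MBF comparisons as secondary.
- Fix both equations before the validation comparison.
- State in section (C) that the components named in the endpoint are kept and that selection applies only among the APCs.
- In the section on APCs and FFR_CT against an invasive FFR standard, call the MPS composite the comparator instead of a gold standard.

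The cost is mainly wording, with a small change to the model-building code. The price is that fewer contrasts can be claimed as primary. Penalised fitting would be an option but is a matter of preference and is not needed to resolve the point.
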